**Objective:**

The aim of this study is to assess the impact of a telerehabilitation platform on stroke patients’ adherence to a rehabilitation plan and on their level of reintegration into normal social activities, in comparison with usual care. The primary outcome is patient adherence to stroke rehabilitation (up to 12 weeks), which is hypothesized to influence reintegration into normal living. Secondary outcomes for patients include functional recovery and independence, depression, adverse events related to telerehabilitation, use of services (up to 6 months), perception of interprofessional shared decision making, and quality of services received. Interprofessional collaboration as well as quality of interprofessional shared decision making will be measured with clinicians.

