### Setting

Five selected sites in Quebec, Canada, will start with a control period (preintervention: usual care) until they independently reach their target sample size; this is expected to take between 12 and 18 months. Participants recruited during this period will belong to the control group. The sites will then enter the intervention period until recruitment completion, which is expected to occur after a further 12 to 18 months. Participants recruited during this second period will belong to the intervention group. Site monitoring will carefully document practices during both trial phases.

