### Primary Outcome

The choice of the primary outcome, patient adherence to the stroke rehabilitation plan at 12 weeks, was identified through a pilot study previously conducted by our research team as the most meaningful outcome and to better document the reason why telerehabilitation might be effective. Adherence to telerehabilitation has been operationalized in many different ways across studies [6,51]. We will define adherence as time spent (in minutes) doing any stroke rehabilitation exercises (online + offline). This includes, but is not limited to, physical, writing, and speech therapy as well as mental health–related exercises recommended by the rehabilitation professional. Online session time will be recorded through the telerehabilitation platform. Offline time will include face-to-face sessions doing rehabilitation as well as time exercising on one’s own as instructed by the rehabilitation professional. Offline sessions completed at home will be captured with the use of a journal and recorded by one of the rehabilitation professionals each week. This monitoring step has been used as a method of quality assurance by other scholars in stroke research [52]. Patients’ adherence to a rehabilitation program will also be measured by the Stroke Rehabilitation Exercise Adherence Measure (StREAM) questionnaire at weeks 4, 6 (to allow for test-retest reliability assessment), and 12 [53]. Moreover, health care professional perception of the participants’ adherence to the rehabilitation program will be evaluated on a numerical 10-point rating scale each week during the intervention period.

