**Patients**			
	Reintegration into normal life	Reintegration to Normal Living Index [54]	Baseline and 12 weeks
	Ability to perform daily activities	Functional Independence Measure [46]	Baseline and 12 weeks
	Participation in shared decision making (SDM)	Questionnaire by Strull et al [55]	Following the establishment of the patient treatment plan
	Decisional conflict	SURE (Sure of myself; Understand information; Risk-benefit ratio; Encouragement) questionnaire [56]	Following the establishment of the patient treatment plan
	Satisfaction with treatment plan	Satisfaction with Decision scale [57]	Following the establishment of the patient treatment plan
	Depression	The Beck Depression Inventory [58]	Baseline, 12 weeks, and 24 weeks
	Satisfaction with health care received	Health Care Satisfaction Questionnaire [59]	12 weeks

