**Health care use**			
		Institut national de santé publique du Québec population questionnaire (section A) [60]	12 and 24 weeks
		Provincial health administrative data	12 and 24 weeks
	Adverse events	Patient’s calendar (collected weekly by a rehabilitation professional): incidence of falls, dizziness, pain (visual analog scale), and fatigue (Borg Rating of Perceived Exertion Scale, 1-10)	Weekly basis up to 12 weeks
	Individual costs	Questionnaire developed by the authors for this study	24 weeks

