### Analyses

Baseline site and participant characteristics will be summarized descriptively. Patient outcomes will be summarized by group and site. Statistical analysis of the data will follow intention-to-treat principles. A linear mixed model will be used, with individuals’ data nested into a study site, to isolate the effect of the intervention on both clinical and process outcomes from other changes that may take place during the trial. Key contextual factors, such as patient’s sex and age, state of employment prior to stroke, stroke severity, concomitant rehabilitation treatments received outside the rehabilitation center, and time since stroke event (in days), will be considered in regression models as potential confounders. Interaction terms will be included in the model for any statistically significant contextual factors. Presence of dichotomous stroke outcomes (eg, dizziness) will be compared between study groups using a chi-square test. Multiple imputation will be considered if missing data represent more than 10% of a given variable. Sensitivity analysis will be conducted to assess the impact of missing data on estimates of intervention effects with a multiple imputation statistical technique and without imputation (ie, available case analyses), as well as for outlying observations.

Interviews and treatment plan meetings will be fully transcribed. A descriptive analytical approach will be used to develop a framework of organizational factors leading to a successful telerehabilitation intervention, both at the patient and professional levels. Audio recordings and transcripts will be reviewed simultaneously to assess validity of the transcription process and will be analyzed using an iterative approach [64]. Data saturation will be determined as defined by Constantinou et al [65]. This will be followed by an intersite analysis to identify what is common between the sites examined and what is specific to certain sites, and to compare the different configurations between sites. Finally, matrices with contextual factors will be generated to identify particular patterns [66].

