## Discussion

### Impact

From a clinical perspective, the use of a telerehabilitation platform will improve adherence to stroke rehabilitation programs by (1) better anchoring patients and families in their own environments (eg, by using day-to-day objects to perform rehabilitation exercises) to favor functional rehabilitation; (2) facilitating an intensive rehabilitation program by decreasing the time and hurdles of traveling; (3) providing an optimal care plan that matches the patient and family condition, context, and expectations; and (4) favoring more active participation by the patient and family as well as by all members of the rehabilitation team.

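### The adverse-event calendar has no baseline reading and rates fatigue on an exertion scale, so symptoms present at entry can pass as new and exercise effort can pass as harm

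*Protocol article*

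**What the plan says.** The Objective in the Abstract names "adverse events related to telerehabilitation" among the secondary outcomes. Table 1 lists one adverse-event instrument, a patient calendar gathered by a rehabilitation professional. It covers "incidence of falls, dizziness, pain (visual analog scale), and fatigue (Borg Rating of Perceived Exertion Scale, 1-10", timed "Weekly basis up to 12 weeks". No baseline is listed for this row.

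Three patient rows of Table 1 do list a baseline: reintegration, functional independence and depression. Depression, for example, is timed "Baseline, 12 weeks, and 24 weeks".

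On analysis, the article says: "Presence of dichotomous stroke outcomes (eg, dizziness) will be compared between study groups using a chi-square test". The sentence does not refer to status at entry. On design, the Setting section has each site finish its control period and then switch: "Participants recruited during this second period will belong to the intervention group".

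Two passages bear on exertion. Primary Outcome: "We will define adherence as time spent (in minutes) doing any stroke rehabilitation exercises (online + offline". Impact, in the Discussion, lists among the expected mechanisms "facilitating an intensive rehabilitation program by decreasing the time and hurdles of traveling".

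**The concern.** There are two separate problems.

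**No reading at entry.** Incidence means new occurrence. Dizziness, pain and fatigue can be present after a stroke before any rehabilitation session. The article itself treats dizziness as a stroke outcome in Analyses, while the Objective presents adverse events as related to telerehabilitation. A calendar that starts with treatment cannot tell a persisting symptom from a new one. Because the groups are consecutive cohorts, nothing in the design balances the share of patients who arrive with the symptom.

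**An exertion scale used for fatigue.** By its own title the Borg scale rates perceived exertion. The intervention aims to raise exercise time and to make an intensive programme easier to deliver. If patients work harder or longer, this score may rise for that reason, and the rise would be filed under adverse events.

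At stake is whether the safety comparison can be interpreted, since no other adverse-event instrument is listed.

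**Working it through.** The plan states no figure for adverse events, so there is nothing to reproduce. The check sets the passages side by side and then illustrates the consequence for a yes/no item such as dizziness. Group sizes of 110 and 220 come from Sample Size Estimates. **All symptom rates and the SD below are assumptions**, and clustering by site is ignored.

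**Side by side.** Table 1 lists seven patient rows before the health-care-use block. Three have a baseline. The other four (participation in decisions, decisional conflict, satisfaction with the plan, satisfaction with care) concern the plan or the care received and have no natural baseline. The relevant contrast is therefore with status scales followed over time: all three list a baseline, and the symptom calendar does not.

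**Formula.** Let q be the share with the symptom at entry and r the risk of new onset among the rest. If every patient who reports the symptom in any week counts, recorded presence = q + (1 − q) × r.

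**Step 1: equal prior prevalence, true doubling of new onset (15% to 30%), q = 40%.**
- Control: 0.40 + 0.60 × 0.15 = 0.49
- Intervention: 0.40 + 0.60 × 0.30 = 0.58
- Recorded ratio: 0.58 / 0.49 = 1.18, against a true 2.0
- Recorded difference: 9 points. New events over the whole cohort: 0.60 × 0.15 = 9% against 0.60 × 0.30 = 18%, also 9 points.

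The ratio shrinks and the absolute difference does not. At q = 20% the recorded rates are 32% and 44% (ratio 1.38); at q = 60% they are 66% and 72% (ratio 1.09).

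**Step 2: power, equal prior prevalence, new onset 10% against 22% (true ratio 2.20).** Power is from a two-sided 5% normal-approximation test of two proportions. The last column restricts the test to patients free of the symptom at entry, 110 × (1 − q) and 220 × (1 − q). That is the fair comparison, because the baseline reading also reduces the number at risk.

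| q | Recorded presence | Recorded ratio | Power, as recorded | Power, new onset only |
|---|---|---|---|---|
| 0% | 10% v 22% | 2.20 | 79% | 79% (110:220) |
| 20% | 28% v 37.6% | 1.34 | 41% | 69% (88:176) |
| 40% | 46% v 53.2% | 1.16 | 23% | 55% (66:132) |
| 60% | 64% v 68.8% | 1.07 | 14% | 38% (44:88) |

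**Step 3: no true effect, but prior prevalence shifts between periods.**
- New onset 15% in both, prior 40% in control against 50% in intervention: 0.40 + 0.60 × 0.15 = 49% against 0.50 + 0.50 × 0.15 = 57.5%, a false difference of 8.5 points. The test rejects about 31% of the time.
- New onset 10% in both, prior 30% against 40%: 0.30 + 0.70 × 0.10 = 37% against 0.40 + 0.60 × 0.10 = 46%. The test rejects about 34% of the time.
- A smaller shift, prior 40% against 45% with 15% new onset: 49% against 53.25%. The test rejects about 11% of the time, against a nominal 5%.
- If prior prevalence falls between periods, the sign reverses and the intervention looks safer than it is.

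**Step 4: exertion.** If mean Borg score were 0.5 to 1 point higher in the intervention group (assumed SD 2), a two-group comparison would detect it with 57% to 99% power. This shows only that an effort-related shift of that size would be visible. The article does not say that such a shift will occur.

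**The case against.** The strongest reply is that the article gives no rule for what counts as an event. Pain and fatigue are scores repeated weekly, no cut-off turns either into an event, and the word incidence may attach only to falls, or to falls and dizziness. A fuller document may define onset, worsening and relatedness, or use the first weekly entry as reference. This stands. A reader might infer that anyone with pain at consent will be logged as an incident case, and that prior symptoms are therefore counted as harm. The article does not say so. It supports only that they can be, and clearly so only for dizziness, whose presence is to be tested. A first weekly entry would not fully repair this, because it falls after treatment starts.

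The arithmetic fits a yes/no item, not pain or fatigue as scored, and its rates are assumed. That also stands. It also follows that dilution affects the ratio and power, not the absolute difference, and the article does not say which measure will be reported.

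A reader might infer that the intervention is meant to make patients exert themselves harder. The article does not establish this: adherence is defined in minutes, and the intensive programme is tied to less travel. A rise in exertion is plausible, not stated.

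A reader might also infer that Table 1 gives most patient measures a baseline. It does so for three of the seven rows, so the argument rests on the status scales alone.

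Finally, changing an instrument partway through the control phase of a before-after design carries its own risk of bias. This is fair, and is why the fix adds items and keeps the Borg item. It does not remove the case for acting, because the instrument and schedule are fixed in the text, and without a reading at entry no later event definition can be applied cleanly.

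**Conclusion.** The point holds in limited form, as a worthwhile and inexpensive improvement to one secondary outcome. Under the stated schedule and test, symptoms present at entry can be counted as incident. With equal prior prevalence the cost is a smaller ratio and lower power: at 40% prior prevalence and 10% against 22% new onset, the ratio is 1.16 instead of 2.20, and power is 23% instead of the 55% available from a new-onset analysis. With a 10-point shift in prior prevalence and no true effect, a false difference of 8.5 to 9 points appears, declared significant about 31% to 34% of the time. A directional bias needs such a shift, or more exercise in the intervention group; neither is shown to exist. These sizes rest on assumed rates, on a yes/no item, and on no clustering.

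The exertion point is one of construct and needs no rates: a perceived-exertion score does not by itself show fatigue as a harm. It does not touch falls.

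**What to change.** 1. At the existing baseline contact, before the first session and in both phases, ask the calendar items once: recent falls, dizziness, pain score and fatigue.
2. Analyse dizziness as new onset among patients without it at entry. Analyse pain and fatigue as change from, or adjusted for, the patient's own baseline.
3. Add to the weekly calendar a simple numerical fatigue rating that refers to time outside exercise.
4. Keep the Borg item unchanged, so that all patients stay comparable on it, but report it as exercise intensity and not as an adverse event.

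The cost is about four questions at a contact that already takes place and one added weekly item. The downside is real but bounded. By July 2021, 37 patients had been enrolled with only control collection under way, which is 37 / 110 = 34% of the planned control group. Patients enrolled before the change will lack the baseline reading and the new fatigue item. A sensitivity analysis should compare results with and without them, and the date of the change should be reported. The intervention phase had not begun, so every intervention patient can have the full set.

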**Patient’s relatives**			
	Quality of services received	Quality of Services Questionnaire for Relatives poststroke [61]	12 weeks
**Rehabilitation professionals**			
	Statistics related to the use of the telerehabilitation platform (who, when, and duration)	Questionnaire developed by the authors for this study	Weekly basis
	Interprofessional collaboration	Assessment of Interprofessional Team Collaboration Scale, short version [62]	Every 3 months for the full duration of the study
	Perception of interprofessional care SDM	Collaboration and Satisfaction About Care Decisions questionnaire [63]	Following the establishment of the patient treatment plan

### Sample Size Estimates

We calculated the sample size for a univariate comparison of the primary outcome between the two study groups at 12 weeks. The required sample size was calculated using G*Power (version 3.1.9.4; Heinrich-Heine-Universität Düsseldorf) based on a conservative estimated effect size of the intervention (Cohen *d*) of 0.4. This sample size was calculated assuming the following: (1) a two-sided type I error probability of 5% and a power of 80%, (2) a duration of 12 weeks, (3) a 2:1 ratio of intervention to control group participants, (4) two study groups, (5) a <5% loss to follow-up, and (6) intracluster correlations of 0.10. Therefore, 330 participants will be recruited: 110 and 220 participants in the control and intervention groups, respectively.

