## Methods

### Study Design

An interrupted time series design with a convergent qualitative component is proposed to test the effectiveness of the intervention. The intervention consists of observing the same dependent variable over time, with a break in the series of observations corresponding to the introduction of an intervention. If the intervention is effective, a change in the series’ pre- and postintervention averages can be observed [45]. Moreover, such design will accommodate pre-existing trends and control for possible variations within and among sites (eg, rehabilitation treatment efficacy, low adherence to treatment plan, and team composition). This study was registered at ClinicalTrials.gov (NCT04440215).

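### The 330-patient sample size implies a design effect of about 1.40, as if five patients formed a cluster, so the stated 80% power is not supported for this five-site before-after design

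*Protocol article*

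**What the plan says.** Sample Size Estimates states what was sized: "We calculated the sample size for a univariate comparison of the primary outcome between the two study groups at 12 weeks". The inputs are "a conservative estimated effect size of the intervention (Cohen *d*) of 0.4", "a two-sided type I error probability of 5% and a power of 80" per cent, "a 2:1 ratio of intervention to control group participants", "a <5% loss to follow-up", and then "6) intracluster correlations of 0.10. Therefore, 330 participants will be recruited: 110 and 220 participants in the control and intervention groups, respectively". No cluster size, design effect or formula is given.

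The design is set out elsewhere in the Methods. Study Design says "An interrupted time series design with a convergent qualitative component is proposed to test the effectiveness of the intervention", and adds that this design allows for trends already under way. Setting says "Five selected sites in Quebec, Canada, will start with a control period", after which each site moves to an intervention period. Analyses specifies a linear mixed model with patients nested in study site. Site is the only clustering unit the article describes.

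**The concern.** The paragraph gives inputs and presents a total as their consequence, so it can be checked. The total implies a much smaller inflation for clustering than an ICC of 0.10 would give with the actual number of patients per site, and the size of that inflation matches the number of sites. The formula also belongs to a trial that puts different sites in different arms. Here every site contributes control patients first and intervention patients later. A stable site effect then cancels from the comparison, and the variance depends on how far site effects shift between phases and on any calendar-time adjustment. Neither quantity appears in the calculation.

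At stake is how the result is read. A null finding would be taken as coming from a trial with 80% power at d = 0.4, when the power could be clearly higher or clearly lower.

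**Working it through.** **Inputs from the article.** d = 0.4 (SD 1), two-sided alpha 0.05, power 0.80, 2:1 allocation, loss taken as 5%, ICC 0.10 (all Sample Size Estimates); five sites (Setting).

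**Step 1: no clustering.** Normal approximation: control n = (1.960 + 0.842)² × (1 + 1/2) / 0.4² = 73.6, so 74 + 148 = 222. The noncentral t version needs 75 + 149 = 224 (power 0.803). Allowing for loss, 224/0.95 = 236.

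**Step 2: implied design effect.** 330 × 0.95 / 224 = 1.40. Setting 1 + (m − 1) × 0.10 = 1.40 gives m = 5.

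**Step 3: reproduce the total.**
- m = 5, normal base: 74 × 1.4 / 0.95 = 109.1, so 110 + 220 = 330, an exact match.
- m = 5, t base: 224 × 1.4 / 0.95 = 330.1. Rounding the control group up first (75 × 1.4 / 0.95 = 110.5) gives 111 + 222 = 333.
- Neighbouring values miss (normal base): m = 4 gives 306 and m = 6 gives 351.

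Actual cluster sizes are 330/5 = 66 per site, or 22 control and 44 intervention if sites are equal (an assumption).

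**Step 4: variance for the design described.** Let CAC be the correlation of a site's effect between its two periods. In SD units, with five equal sites,

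variance = (1 − ICC)(1/n0 + 1/n1) + 2 × ICC × (1 − CAC)/5.

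After 5% loss, n0 = 104.5 and n1 = 209 (about 313 patients). The first term is 0.9 × (0.00957 + 0.00478) = 0.0129. The second is 0.04 × (1 − CAC). The article gives no CAC, so the values below are assumptions.

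| CAC | Variance | SE | Power, normal | Power, t on 4 df |
|---|---|---|---|---|
| 1.0 | 0.0129 | 0.114 | 94% | 75% |
| 0.8 | 0.0209 | 0.145 | 79% | 55% |
| 0.5 | 0.0329 | 0.181 | 60% | 39% |

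**Step 5: add a common linear calendar trend.** Assume uniform accrual within each phase, a shared switch date and stable site effects. With phase lengths L0 and L1 and two-thirds of patients in the second phase, the variance of the intervention step is multiplied by 1 + B/W, where B = (2/9) × ((L0 + L1)/2)² and W = (1/3)L0²/12 + (2/3)L1²/12. Working in years:
- 12 then 24 months: B = 0.500, W = 0.250, inflation 3.00.
- Equal phases (per unit of phase length): B = 0.222, W = 0.0833, inflation 3.67.
- 18 then 12 months: B = 0.347, W = 0.118, inflation 3.94.

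Applied to 0.0129, the SEs are 0.197, 0.218 and 0.226. Power at d = 0.4 is 53%, 45% and 43%. The effect detectable with 80% power (2.80 × SE) is 0.55, 0.61 and 0.63 SD.

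**The case against.** **The cluster size is inferred.** The article does not print 5. Other routes come near 330, such as m = 6 with no allowance for loss (333-339) or 90% power with about a 10% inflation (327-336). Loss is stated as below 5%, and the exact 110/220 match uses the normal base although the article names G*Power. This stands as a limit on certainty. The alternatives that were tried, however, each drop or change a stated input, and 5 coincides with the only cluster count in the article.

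**330 may be adequate.** This also stands. Under the formula in Step 4 with a normal test and no time term, power reaches 80% at a CAC of about 0.81 and 94% with stable sites. A reader might infer that no sound use of ICC 0.10 leads to 330. That goes too far: the paragraph does not justify the 80%, but a particular between-period correlation could.

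**The trial might look several times too small.** A reader might put 66 into the parallel-cluster formula, get 1 + 65 × 0.10 = 7.5, and conclude that far more patients are needed. The documents do not support this, because Setting has every site running both phases and that formula describes a different design.

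**The low figures rest on choices the article does not make.** Analyses names no explicit calendar-time term and no degrees-of-freedom method, so the 43-53% and the 4-df column are conditional. A flat statement that power is about one half would overreach. Even so, Study Design claims control of existing trends, and Analyses says the model is meant to separate the intervention from other changes over the trial. If a time term delivers that, the cost is of the size shown.

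**Sizing on a simpler test than the analysis is common and is declared here.** That is true and is not an error in itself. It does not explain the size of the clustering adjustment.

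**Conclusion.** The point holds in this form: 330 follows from the stated inputs only with a design effect of about 1.40, a cluster size of about 5 where sites average about 66 patients, and the formula does not fit a design in which each site supplies both groups. The stated 80% power is unsupported in either direction.

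At d = 0.4 and ICC 0.10, without a time term, normal-approximation power runs from about 94% down to 60% as the CAC goes from 1 to 0.5 (75% to 39% on 4 df). With a common linear trend and stable sites it is about 43-53%, and the effect detectable with 80% power is about 0.55-0.63 SD.

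These figures rest on equal sites, 5% loss, assumed CAC values and, for the trend case, uniform accrual and the phase lengths listed. That the number of sites was used as the cluster size is a strong inference from the arithmetic, but the article does not state it.

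**What to change.** Keep 330 patients and rewrite the paragraph in Sample Size Estimates:

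- Define the cluster, and give the expected number of patients per site and phase.
- Replace the calculation with one for the planned within-site before-after mixed model, using variance = (1 − ICC)(1/n0 + 1/n1) + 2 × ICC × (1 − CAC)/5.
- State a range for the CAC, the reference distribution to be used with five sites, and the variance inflation for any calendar-time term in the model.
- Report power at d = 0.4, or the effect detectable with 80% power, as a range in place of the single 80%.

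The cost is one paragraph and a stated power that may be less favourable. No extra patients are needed. The Results section says analysis will not begin before data collection ends, so the correction can be made before any outcome analysis.

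### The 330 patients rest on an implied cluster size of about 5 that matches no cluster in the trial, so the stated 80% power with ICC 0.10 is not a property of this design

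*Protocol article*

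**What the plan says.** Sample Size Estimates in the protocol article sizes a two-group comparison of the primary outcome at 12 weeks. The inputs are listed one by one:

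- the effect size: "based on a conservative estimated effect size of the intervention (Cohen *d*) of 0.4"
- the error rates: "a two-sided type I error probability of 5% and a power of 80" percent
- the allocation: "3) a 2:1 ratio of intervention to control group participants"
- the loss: "5) a <5% loss to follow-up"
- the clustering, with the result drawn directly from the list: "6) intracluster correlations of 0.10. Therefore, 330 participants will be recruited: 110 and 220 participants in the control and intervention groups, respectively"

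No cluster size or design effect is given.

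Two other sections define the structure. Setting says "Five selected sites in Quebec, Canada, will start with a control period", after which the same sites move to the intervention period. Analyses names the study site as the level in which patients are nested in the linear mixed model.

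**The concern.** The paragraph presents 330 as the consequence of its listed inputs, one of which is an ICC. An ICC affects a sample size only through a cluster size and a design. The cluster size needed to arrive at 330 is about 5, and no cluster of that size appears in the document. The type of inflation needed belongs to trials in which a whole cluster is in one arm, which is not the case here.

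This is the only justification of the trial's size that the article gives. If the 80% does not describe the actual design, a reader of a null result cannot tell which effects it makes unlikely. The detectable effect could be near d = 0.32 or near d = 0.64, depending on a quantity that the calculation does not use.

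**Working it through.** **Inputs from the document.** d = 0.4, two-sided α = 0.05, power 80%, 2:1 allocation, loss below 5% (5% used), ICC 0.10, N = 330 (Sample Size Estimates); five sites, each contributing to both periods (Setting); clustering by site (Analyses). **Assumptions.** Equal site sizes, so 330/5 = 66 patients per site (22 control, 44 intervention), and d expressed on the total SD.

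**Step 1: reproduce 330.** With the noncentral t distribution, 75 + 149 = 224 patients give power 0.803. The normal approximation gives 222, and exact 2:1 with the t distribution gives 225. The implied design effect is

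330 × 0.95 / 224 = 1.40, so m = 1 + (1.40 − 1)/0.10 = 5.

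Forward, N = 224 × [1 + (m − 1) × 0.10] / 0.95:

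| m | Design effect | N |
|---|---|---|
| 4 | 1.3 | 307 |
| 5 | 1.4 | 330 |
| 6 | 1.5 | 354 |
| 22 (control patients per site) | 3.1 | 731 |
| 44 (intervention patients per site) | 5.3 | 1,250 |
| 66 (all patients per site) | 7.5 | 1,768 |

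Starting from 222 or 225 instead of 224, m = 5 gives 327 to 332. With the listed inputs and this formula, only m of about 5 returns 330. The last three rows show that none of the trial's real cluster sizes does. They are not sample sizes that this trial needs.

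**Step 2: the form that fits the design.** Each site is compared with itself. Let r be the correlation between a site's effects in the two periods. With total variance 1 and within-period ICC 0.10, the variance of the estimated difference is

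V = 0.90 × (1/n₀ + 1/n₁) + 2 × 0.10 × (1 − r)/5.

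After 5% loss, n₀ = 104.5 and n₁ = 209. The first term is 0.90 × 0.014354 = 0.01292 and the second is 0.04 × (1 − r). Normal-theory power is Φ(0.4/√V − 1.96), and the effect detectable with 80% power is 2.80 × √V.

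| r | V | Power at d = 0.4 | Detectable d |
|---|---|---|---|
| 1.0 | 0.01292 | 94% | 0.32 |
| 0.9 | 0.01692 | 87% | 0.36 |
| 0.8 | 0.02092 | 79% | 0.41 |
| 0.5 | 0.03292 | 60% | 0.51 |
| 0 | 0.05292 | 41% | 0.64 |

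The document does not give r, so the table is a range.

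**Step 3: two things the table leaves out.** These are large-sample figures without a time trend.

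- With five sites, a test on 4 degrees of freedom has about 75% power even at r = 1.
- A linear time trend, with uniform recruitment assumed over 15 + 15 or 15 + 30 months, multiplies the variance by 3.63 or 2.98. Power at r = 1 after 5% loss is then about 45% or 53%.

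**The case against.** The strongest reply is that 330 may be adequate. With perfectly stable site effects the trial exceeds 80% power, and with a between-period correlation of about 0.8 it has almost exactly 80%. This stands. A reader might infer from the mismatch that 330 patients fall short of 80%, or that no correct use of ICC 0.10 is compatible with 330. The documents support neither. Because the calculation neither states nor uses a between-period correlation, the agreement near 0.8 is a coincidence and does not justify the stated figure.

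A reader might also put 66 in place of 5 and conclude that 1,768 patients are needed, or that power is about 22%. Those figures apply only if whole sites were allocated to one arm. Setting rules that out.

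The mechanism is also uncertain. Five is the number of sites, so a swap of number of clusters for cluster size is the obvious explanation, but it is an inference. Other routes to 330 exist if the stated inputs are abandoned: 90% power without clustering needs 297 patients, and 297/0.90 = 330 with 10% loss. The mismatch does not depend on which explanation is right.

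Finally, a journal article may leave the cluster size and design effect to the full protocol, so their absence alone is no finding. The point is narrower: the article lists its inputs, draws the conclusion, and that conclusion does not follow for the design it describes.

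**Conclusion.** The point holds as a wrong planning figure. It does not show that the trial is too small. Under the usual inflation, 330 requires a design effect of about 1.4 and a cluster of about 5 patients, against five sites of about 66, and that inflation does not suit sites that contribute to both groups. The stated 80% power with ICC 0.10 is therefore not a property of this design.

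With the within-site calculation, power at 330 lies between about 41% and 94% as the between-period site correlation goes from 0 to 1, and is 79% at 0.8. This rests on equal sites, d on the total SD, 5% loss, no time trend and normal theory. The 94% should not become the new headline: it needs perfectly stable site effects, no trend adjustment and a test that ignores having only five sites. Study Design says that the design will accommodate existing trends, so a no-trend figure is an optimistic bound.

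**What to change.** Keep N = 330. In Sample Size Estimates, remove the 1.4 inflation and the claim of 80% power with ICC 0.10. Replace them with a within-site before/after calculation that:

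- names the site as the cluster and gives the expected patients per site and period;
- states the within-period ICC (0.10) and a range for the between-period site correlation;
- reports power and detectable d over that range (94%, 87%, 79%, 60% and 41% at correlations 1.0, 0.9, 0.8, 0.5 and 0; d about 0.32 to 0.64);
- says that these are no-trend, large-sample figures, and that both the small number of sites and any adjustment for a time trend lower them.

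The cost is one rewritten paragraph and a short recalculation, with no extra patients. At the time of the article 37 patients had been enrolled and analysis was not planned before the end of data collection, so the change can be made before any outcome comparison.
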